**Inclusion criteria**
Personal smartphone (either Android or iPhone iOS).Clearance from the primary care provider.At-risk noncommunicable disease and confirmed by in-person evaluation.Willingness to participate.No contraindications to participating in treatment recommendations.
**Exclusion criteria**
Diagnosis of stage IV cancer or any other advanced malignant disease.Acute osteomyelitis or acute bone disease.Present or past DSM-5 (*Diagnostic and Statistical Manual of Mental Disorders* [Fifth Edition]) diagnosis of schizophrenia, delusional disorder, psychotic disorder, or dissociative disorder that would be judged to interfere with study participation.Pregnancy.Any clinically unstable systemic illness judged to interfere with treatment.Any condition requiring urgent surgery or a procedure.An active substance use disorder, such as cocaine or IV heroin use that would interfere with study participation.

#### Study Risks

The risks of participation in this study are minimal, mainly because the clinician will make all the treatment decisions. All treatment that the participants receive will be standard-of-care treatment that any patient with the same diagnosis would receive. Although the risk is low, the participants’ data and communications could be breached. As both platforms are online, the risk of unauthorized viewing or use of online data is higher than that of physical records. The entire platform will be hosted within a HIPAA-compliant firewall, and the smartphone patient-facing app will be compliant with all relevant standards to maintain patient confidentiality. The MobileNetrix app has been used previously in clinical trials conducted at Mass General Brigham and is Veracode tested. Finally, participants may become uncomfortable and emotional while completing some of the questionnaires. Risks of AI include unrecognized biases and hallucinations, leading to the potential of erroneous decision support recommendations.

#### Enrollment Procedures

The smartphone will be used to communicate with the eligible participants. They will be sent a poll using an SMS text messaging–based survey app for eligibility for in-person evaluation. The administrative portal will automatically categorize participants into a defined level of risk of their NCD. The participants with confirmed NCDs will be evaluated by the interdisciplinary team noted above, and a personal treatment regimen will be designed for them to reduce their health risks, along with a DT that reflects their state of health at enrollment. There will also be a comparison-matched group of participants who will be randomized to a treatment-as-usual condition, where they will not have access to the DT technology. After sufficient instruction, the participants in the experimental treatment condition will be tracked daily and be provided with reinforcing messaging and automated problem-solving based on their DT. Any changes in their health-related behaviors will automatically be reflected in an updated DT. Efficacy of the DT and personalized medicine approach will be measured by the number of individuals reaching a 37% risk reduction, with comparison between enhanced care using the DT and treatment as usual (TAU). TAU is defined as the treatment of one of the study’s NCDs using published guidelines and literature as a guide, but without using any of the DT study interventions. Secondary outcome measures that will be tracked will include each of the diagnosed NCD risk factors and other outcome measures, including compliance and helpfulness ratings of the participants and treating providers. In addition to studying the 3 NCDs noted above, we will select patients diagnosed with type II diabetes with pain for further in-depth analysis, as detailed in the Statistical Methods section.

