If the risk factors are confirmed, an additional evaluation will be used to determine other specific risk factors associated with that condition, including level of physical activity, psychological traits or maladaptive behaviors, and barriers to improvement, including the presence of pain, sleep disruption, smoking, and other comorbidities related to worsening health. For an overview of these inputs, refer to Table S2 in Multimedia Appendix 1. These secondary domains will become the individual’s study-specific targets. All of these factors will be incorporated into the participant’s DT. The DT will be shared with the patient through the study app and reviewed with the patient during an in-person follow-up visit. The study platform will provide daily questionnaires that are specific to each NCD category and problem list. Objective tracking of the patient’s activity level and physiological measures (such as blood pressure, glucose levels, and pulse oximetry) will continue throughout the treatment period. All these daily data points will be used to update the DT and will appear in the participant’s study portal that is part of the patient-facing app. The updated DT primary endpoint will reflect the change in health risk. Participants found not to be compliant with the program will be contacted and interviewed regarding barriers and their impressions of the program. Clinician decision-making will also be tracked. Variance from DT treatment recommendations and the impact on NCD risk factors will be reviewed and statistically compared to expected outcomes from relevant evidence-based literature.

Automated contextual daily motivational messaging that aligns with the participant’s behavioral traits will continue throughout the study period. Daily compliance reminders for medication regimens will be incorporated into the study app. The program goal will be a 37% reduction in long-term health risk from baseline as determined by the NCD-specific risk questionnaire (Tables S1 in Multimedia Appendix 1). This is considered to be a meaningful reduction in health risk using the financial modeling included in this reference that will sustain a DT program [93]. The number of participants in each arm reaching this goal will be used to evaluate the primary objective of this study as noted above. Each candidate will be followed for 6 months, and the study length will be determined by enrollment rate.

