In our previous work [85,95-97], we had a high rate of consent to participate among recruited patients, with minimal attrition. We assessed power based on our preliminary data and previously published studies. The power analysis revealed that a sample size of 100 participants (50 per treatment arm) using a 2-sample *t* test for a difference in mean pre/post change score gives the study a >85% probability of detecting a 1.5-point group difference on a 0‐10 rating scale (assuming an SD of 1.8). Conventional metrics suggest that a 30% change or difference score is clinically meaningful [98], and this sample size would provide adequate power to detect a group difference of approximately 20%. Most of the analyses in the proposed study will involve delta scores reflecting changes within participants (both uncorrected and adjusted least squares). We will examine the distribution of the delta scores between treatment arms and ascertain whether that distribution was normal for each of the study variables. Parametric (eg, analysis of covariance) or nonparametric analyses will be used on the variables based on whether the variables were numeric or categorical and showed normal distributions. Collectively, this sample size (N=100), together with our previously observed very high retention rates and the substantial efficacy of the platform, will provide more than adequate power to detect moderate-size effects. Participants will be randomized to the DT and TAU groups with equal allocation. The primary outcome measure will be the Patient Global Impression of Change (PGIC), which represents the participant’s overall belief about the efficacy of treatment on a 7-point categorical verbal rating scale. The scale ranges from (1) “no change or condition has gotten worse” to (7) “a great deal better and a considerable improvement that has made all the difference.” There will be prespecified secondary efficacy measures. Pain severity and pain interference with function will be evaluated with the Brief Pain Inventory. Neuropathic pain was assessed with the 7-item painDETECT questionnaire*.* Pain-related disability was evaluated with the Pain Disability Index. Psychological outcomes included the Hospital Anxiety and Depression Scale and the Pain Catastrophizing Scale. These outcome measures have been widely used in prior treatment trials, and their psychometric properties have been validated in US patients with chronic pain. All instruments were delivered via REDCap (Research Electronic Data Capture; Vanderbilt University). All efficacy measures, except for PGIC, will be taken at baseline and 3 months. PGIC will be assessed at 3 months.

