
The sample size calculation will be designed to confirm the hypothesis that the treatment assigned to the DT group will be associated with a greater PGIC score compared to the TAU control group at 3 months of 0.6 points with an SD of 1.0. The calculation assumes 85% power and a 2-sided type I error rate of 0.05. The estimated sample size of 100 will be increased to a target recruitment of 115 to account for 15% drop-out. The primary analysis of treatment effects will be conducted in the intention-to-treat (ITT) population, which will include all randomized participants. In addition, a prespecified subgroup analysis will be carried out. The study protocol predicts that participants in the DT group will demonstrate the greatest treatment effects.

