Responder rates will be compared between treatment groups using logistic regression. Missing outcomes due to study withdrawal will be treated as nonresponders. The dependent variable in the model will be a binary variable indicating whether the participant was a responder or nonresponder. The model includes treatment assignment as an independent variable and baseline pain severity (Brief Pain Inventory average pain item) as a covariate. An interaction term between treatment and baseline pain sensitivity will be added for subgroup analyses of responder rates.

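### The sample size and the 85% power figures are derived for differences in means and do not cover the 37% risk-reduction count by which the plan judges efficacy

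*Protocol article*

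**What the plan says.** Two sections make a binary count the test of success. Validation Methodology for a DT NCD sets a 37% reduction in long-term health risk as the program goal and continues: "The number of participants in each arm reaching this goal will be used to evaluate the primary objective of this study as noted above". Enrollment Procedures says that efficacy "will be measured by the number of individuals reaching a 37% risk reduction, with comparison between enhanced care using the DT and treatment as usual".

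Statistical Methods contains two sizing statements, both for means:

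- For a change score: "a sample size of 100 participants (50 per treatment arm) using a 2-sample" *t* test is said to give more than 85% "probability of detecting a 1.5-point group difference on a 0‐10 rating scale (assuming an SD of 1.8"). The preceding paragraph names the activity interference subscale of the BPI as the measure for the power calculation.
- For PGIC: a higher score in the DT group "compared to the TAU control group at 3 months of 0.6 points with an SD of 1.0", at 85% power and two-sided 0.05. This gives 100 participants, raised to 115 for drop-out.

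The section also claims, without naming an outcome, that N=100 is amply powered for effects of moderate size. It calls the BPI a primary outcome in one paragraph and PGIC the primary outcome in the next. Later it states: "Responder rates will be compared between treatment groups using logistic regression". It assumes no rates there and does not define a responder.

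**The concern.** A power figure belongs to one outcome, one effect and one test. Here the only printed figures belong to two comparisons of means, while the criterion said to decide efficacy is a comparison of two proportions. The figures do not transfer. Cutting a change score at a threshold discards information, so for the same underlying shift a count has less power than the mean. The health-risk measure is also a different instrument from either the BPI or PGIC, and the plan states no effect for it.

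What is at stake is interpretation. If the two arms do not differ clearly in the number reaching 37%, a reader of this protocol would take that as a negative result from a trial with 85% power. The document gives no basis for that reading.

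**Working it through.** **1. Reproduce the plan's own figures.** The inputs come from Statistical Methods, with two-sided 0.05 and equal allocation.

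PGIC: d = 0.6/1.0 = 0.6. The normal formula gives n per arm = 2(1.960 + 1.036)²/0.6² = 49.9, so 50. Power at 50 per arm is Φ(0.6·√25 − 1.960) = Φ(1.040) = 85.1%; with the noncentral *t* it is 84.4%. N=100 is reproduced.

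BPI: d = 1.5/1.8 = 0.833. Power at 50 per arm is Φ(0.833·√25 − 1.960) = Φ(2.207) = 98.6% (noncentral *t* 98.5%). That agrees with the stated figure of more than 85%. These inputs alone would need 26 per arm for 85%, so PGIC is the calculation that matches N=100.

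Neither printed figure is wrong. Both are for means.

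**2. What 50 per arm can detect for a count.** This step needs no assumption about an underlying effect. It assumes that the same 50 per arm is the denominator. For rates p₀ (TAU) and p₁ (DT), with p̄ their average:

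power = Φ{ [ (p₁ − p₀) − 1.960·√(2p̄(1−p̄)/n) ] / √( (p₀(1−p₀) + p₁(1−p₁))/n ) }

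Example, 20% against 48%: p̄ = 0.34; null SE = √(2·0.34·0.66/50) = 0.0947; alternative SE = √((0.1600 + 0.2496)/50) = 0.0905. Then (0.28 − 0.1857)/0.0905 = 1.042, and Φ(1.042) = 85.1%.

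Solving for 85% power:

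| TAU rate | DT rate needed | Gain (points) |
|---|---|---|
| 10% | 34.6% | 24.6 |
| 20% | 47.9% | 27.9 |
| 30% | 59.3% | 29.3 |
| 50% | 78.3% | 28.3 |

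A doubling from 20% to 40% has 59% power.

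**3. Illustration under the plan's two effect sizes.** Assumptions: the underlying change in risk is normal with equal SD in both arms, the 37% goal is a cut-off on it, and the shift equals one of the plan's two standardised effects. The plan supports neither transfer, so both are shown. The DT rate is p₁ = 1 − Φ(Φ⁻¹(1 − p₀) − d). For p₀ = 0.20 and d = 0.6: 1 − Φ(0.842 − 0.6) = 0.405.

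| TAU rate | DT rate, d = 0.6 | Power | DT rate, d = 0.833 | Power |
|---|---|---|---|---|
| 10% | 24.8% | 49.6% | 32.7% | 80.0% |
| 20% | 40.5% | 60.8% | 49.7% | 88.8% |
| 30% | 53.0% | 65.0% | 62.1% | 90.9% |
| 38.2% | 61.8% | 65.9% | 70.3% | 90.9% |
| 50% | 72.6% | 64.3% | 79.8% | 88.9% |

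Over all cut-offs the maximum is 65.9% for d = 0.6 and 91.0% for d = 0.833. In each case the count falls below the mean comparison at the same effect (about 85% and 98.5%).

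**4. Sensitivity to drop-out.** The target of 115 gives about 57 per arm. With no missing data, the best-case power at d = 0.6 is 71.8%. If 15% are counted as nonresponders, it is 58.3% at d = 0.6 and 85.2% at d = 0.833.

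**The case against.** The strongest reply is that the protocol never claims 85% for the count. It attaches 85% to PGIC and more than 85% to a difference on a 0–10 scale, and both figures reproduce. If PGIC is the primary outcome, as the sample-size and main-analysis paragraphs imply, an unsized responder count would be an ordinary secondary outcome. This stands in part: there is no arithmetic error in the printed figures. It does not remove the point, because two sections still say that the count decides efficacy and the primary objective, and the general claim of ample power is not limited to means.

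A reader might infer that power for the count is at most about 66%. The documents do not support that as a ceiling. It carries the PGIC effect, a 3-month global rating, over to a different measure. The plan's other effect, used in the same way, gives up to 91%.

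Two further cautions stand. First, the logistic regression of responder rates adjusts for baseline pain severity and leaves the responder undefined, so it cannot be taken as the test of the 37% count. Second, Enrollment Procedures refers to Statistical Methods for an in-depth analysis of patients with type II diabetes and pain, and that section assesses efficacy at 3 months, whereas Validation Methodology follows participants for 6 months. That the 50 per arm is the denominator for the count is therefore a reading, not a stated fact.

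**Conclusion.** The point holds in limited form. The plan gives no power for the 37% count, and none can be derived from it. The printed 85% and more than 85% do not apply to the count, and the unrestricted statement of ample power for moderate effects is not true for it.

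The firmest statement of size uses no latent model: with 50 per arm in that comparison, 85% power requires a gain of about 25 to 30 percentage points. The ranges of about 50–66% (0.6 SD) and about 80–91% (0.833 SD), for TAU rates of 10–50%, depend on effects borrowed from other outcomes and on a normal underlying change.

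A reader might go on to conclude that a real benefit of the planned size would be missed at least one time in three. That does not follow, because no effect on health risk is planned anywhere in the document.

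**What to change.** 1. Reconcile which outcome is primary: the 37% count, the BPI or PGIC.
2. In Statistical Methods, restrict the 85% and more than 85% figures, and the general claim of ample power, to the comparisons of means.
3. For the 37% count, state its denominator. If that is 50 per arm, add that 85% power requires a difference of about 25 to 30 percentage points (for example 20% against 48%). Report the count as a difference in proportions with a 95% confidence interval.
4. If the count is kept as the primary test, base its stated power on assumed responder rates in each arm, and check N against them.
5. Print no power percentage for the count without the effect it assumes. Refer to the logistic regression as its test only if a responder is defined as reaching the 37% goal.

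If the count is not the primary test, the cost is wording only, and the stated power for the count becomes less favourable. If it is, the sample size may have to be reconsidered once rates are assumed.

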#### Statistical Methods

We expect that both groups (DT Experimental and TAU Control) will have missing data. We will assess whether missing data are more prevalent in one group or the other, and if there are differences among those who drop out early and those who complete the 6-month trial. We will also use corrections for multiple comparisons to reduce the likelihood of type I error (Benjamini-Hochberg correction). A calculation will be produced to determine whether the significance value to interpret statistical significance needs to be different from the standard *P<*.05. Power calculations, as outlined by Cohen [94], will be performed to determine the probability of detecting clinically significant differences between treatment conditions in the primary area of measurement. These calculations will assume a 2-tailed test and α level of .05 that use of a DT will improve activity interference on the activity subscale of the Brief Pain Inventory. The Brief Pain Inventory was chosen as a primary outcome measure. This is because persistent pain and other symptoms are often associated with NCDs that can adversely affect quality of life. The Brief Pain Inventory includes 7 items that assess the degree to which pain and other symptoms interfere with daily living and activity, including general activity, walking ability, normal work (both outside the home and housework), relations with others, sleep, mood, and enjoyment in life (0=does not interfere; 10=completely interferes). These items can be collapsed and averaged into one measure of interference.

In our previous work [85,95-97], we had a high rate of consent to participate among recruited patients, with minimal attrition. We assessed power based on our preliminary data and previously published studies. The power analysis revealed that a sample size of 100 participants (50 per treatment arm) using a 2-sample *t* test for a difference in mean pre/post change score gives the study a >85% probability of detecting a 1.5-point group difference on a 0‐10 rating scale (assuming an SD of 1.8). Conventional metrics suggest that a 30% change or difference score is clinically meaningful [98], and this sample size would provide adequate power to detect a group difference of approximately 20%. Most of the analyses in the proposed study will involve delta scores reflecting changes within participants (both uncorrected and adjusted least squares). We will examine the distribution of the delta scores between treatment arms and ascertain whether that distribution was normal for each of the study variables. Parametric (eg, analysis of covariance) or nonparametric analyses will be used on the variables based on whether the variables were numeric or categorical and showed normal distributions. Collectively, this sample size (N=100), together with our previously observed very high retention rates and the substantial efficacy of the platform, will provide more than adequate power to detect moderate-size effects. Participants will be randomized to the DT and TAU groups with equal allocation. The primary outcome measure will be the Patient Global Impression of Change (PGIC), which represents the participant’s overall belief about the efficacy of treatment on a 7-point categorical verbal rating scale. The scale ranges from (1) “no change or condition has gotten worse” to (7) “a great deal better and a considerable improvement that has made all the difference.” There will be prespecified secondary efficacy measures. Pain severity and pain interference with function will be evaluated with the Brief Pain Inventory. Neuropathic pain was assessed with the 7-item painDETECT questionnaire*.* Pain-related disability was evaluated with the Pain Disability Index. Psychological outcomes included the Hospital Anxiety and Depression Scale and the Pain Catastrophizing Scale. These outcome measures have been widely used in prior treatment trials, and their psychometric properties have been validated in US patients with chronic pain. All instruments were delivered via REDCap (Research Electronic Data Capture; Vanderbilt University). All efficacy measures, except for PGIC, will be taken at baseline and 3 months. PGIC will be assessed at 3 months.

The sample size calculation will be designed to confirm the hypothesis that the treatment assigned to the DT group will be associated with a greater PGIC score compared to the TAU control group at 3 months of 0.6 points with an SD of 1.0. The calculation assumes 85% power and a 2-sided type I error rate of 0.05. The estimated sample size of 100 will be increased to a target recruitment of 115 to account for 15% drop-out. The primary analysis of treatment effects will be conducted in the intention-to-treat (ITT) population, which will include all randomized participants. In addition, a prespecified subgroup analysis will be carried out. The study protocol predicts that participants in the DT group will demonstrate the greatest treatment effects.

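### The primary outcome is designated inconsistently across three measures (37% risk reduction, Brief Pain Inventory, PGIC), and no hierarchy or alpha rule links them

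*Protocol article*

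**What the plan says.** Three measures carry primary status in different parts of the protocol article.

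- **37% risk reduction.** Validation Methodology for a DT NCD states: "The updated DT primary endpoint will reflect the change in health risk". After setting the 37% goal it adds: "The number of participants in each arm reaching this goal will be used to evaluate the primary objective of this study as noted above". Enrollment Procedures repeats this: "Efficacy of the DT and personalized medicine approach will be measured by the number of individuals reaching a 37% risk reduction".
- **Brief Pain Inventory (BPI).** Statistical Methods states: "The Brief Pain Inventory was chosen as a primary outcome measure". A power statement on a 0-10 scale follows (difference 1.5, SD 1.8, 50 per arm, more than 85% power).
- **PGIC.** Later in Statistical Methods: "The primary outcome measure will be the Patient Global Impression of Change (PGIC". The sample size follows (difference 0.6, SD 1.0, 85% power, two-sided 0.05, N=100 raised to 115). The text next to it makes the BPI secondary: "There will be prespecified secondary efficacy measures. Pain severity and pain interference with function will be evaluated with the Brief Pain Inventory".

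On error control, Statistical Methods names Benjamini-Hochberg without saying which tests it covers, then says: "A calculation will be produced to determine whether the significance value to interpret statistical significance needs to be different from the standard" P<.05. Further on, it declares comparisons significant at a two-sided P below .05 and mentions multiplicity adjustment only for secondary efficacy measures.

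**The concern.** A confirmatory trial needs one test, or a stated rule across several tests, that decides whether it succeeded. Here a reader can find textual support for any of three outcomes. If they disagree, the document does not say which one decides, and the designation could be settled after the results are known.

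The choice matters because the three measure different things. The 37% count concerns long-term health risk, the stated program goal. PGIC records the participant's belief about how well treatment worked, and participants in the treatment-as-usual arm have no access to the digital twin. A favourable PGIC with a null risk result could be presented as validating the platform, and nothing in the text rules that out. The outcome closest to the health claim is also the one with no power statement.

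**Working it through.** **1. The plan's own sample size (PGIC).** Inputs from Statistical Methods: difference 0.6, SD 1.0, power 85%, two-sided alpha 0.05, equal allocation.

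n per arm = 2 × [SD × (z₀.₉₇₅ + z₀.₈₅) / difference]² = 2 × [1.0 × (1.960 + 1.036) / 0.6]² = 49.9, so 50 per arm and 100 in total. The stated figure reproduces. With the noncentral t distribution, power at 50 per arm is 84.4%, which is close enough.

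**2. The BPI power statement.** SE = 1.8 × √(2/50) = 0.36. Power = Φ(1.5/0.36 − 1.960) = Φ(2.21) = 98.6%, consistent with more than 85%.

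Both calculations spend a full two-sided 0.05, so neither reserves alpha for the other or for the 37% count.

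**3. Chance of at least one false positive if success could be claimed on any of the three.** Correlations are assumptions; the document says only that moderate correlations are expected among many of the efficacy measures. The figures at correlations 0.3 and 0.5, and those under Benjamini-Hochberg, come from simulating one million trivariate normal draws.

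| Rule | Correlation 0 | 0.3 | 0.5 |
|---|---|---|---|
| Each tested at .05 | 1 − 0.95³ = 14.3% | 13.6% | 12.5% |
| Benjamini-Hochberg over all three | 5.0% | 4.9% | 4.7% |

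The text does not say which row applies.

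**4. What splitting alpha would do.** With an equal three-way split (0.05/3 = 0.0167), PGIC power at 50 per arm falls to 72.8%, and 85% power needs 66 per arm. So N=100 is right for PGIC as the single primary at .05, but not for three primaries sharing alpha.

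**5. Power for the 37% count.** The document gives no control rate, so the rates below are assumptions. Power = Φ[(d − 1.960 × SE₀) / SE₁], with SE₀ from the pooled and SE₁ from the separate proportions, 50 per arm. Example, 30% v 50%: SE₀ = √(0.4 × 0.6 × 2/50) = 0.0980; SE₁ = √[(0.21 + 0.25)/50] = 0.0959; power = Φ[(0.200 − 0.192)/0.0959] = 53%.

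| Assumed control rate | Power for a 20-point difference | Difference detectable at 85% power |
|---|---|---|
| 10% | 71% | about 25 points |
| 20% | 59% | about 28 points |
| 30% | 53% | about 29 points |
| 40% | 52% | about 29 points |

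**6. Analysis and timing.** The logistic regression of responder rates at the end of Statistical Methods does not define a responder and adjusts for baseline pain severity, so it is not tied to the 37% goal. PGIC is read at 3 months, and the other efficacy measures listed with it at baseline and 3 months. Follow-up is 6 months, and the 37% count has no stated assessment time.

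**The case against.** The strongest reply is that PGIC is plainly the intended primary. It alone is called the primary outcome measure with the definite article, and it alone has a stated hypothesis, a sample size with a dropout allowance, and an analysis text that sets it apart from the secondary measures. The 37% count is never literally called a primary outcome measure; its status comes from the wording on primary endpoint, primary objective and efficacy. This makes PGIC the likeliest intention, but it does not cancel the sentences that say otherwise.

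A reader might infer that the trial plans three unadjusted primary tests and so carries a 14.3% false positive rate. The documents do not support that. Benjamini-Hochberg is stated without restriction to secondary measures; over all three tests it would hold the chance of any false positive near 5% when no effect exists. The .05 rule follows the mixed-model text and is not tied to the 37% count. The 14.3% is therefore an upper bound. Nor do the three measures all have different analyses: PGIC and the BPI change score share the same mixed model.

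Another reading is possible. Enrollment Procedures promises an in-depth analysis of type II diabetes patients with pain, detailed in Statistical Methods, whose instruments are largely pain measures. PGIC and the BPI might belong to that subset, with the 37% count as the whole-trial outcome. Statistical Methods never says so, and its primary analysis takes in everyone randomized. If it were the intent, the main trial would have no sample size justification.

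**Conclusion.** The point holds as a contradiction within the text, not as detail left to an analysis plan. Primary status is given to the 37% count in substance, to the BPI by name (and then withdrawn), and to PGIC by name, with no hierarchy or alpha rule. The arithmetic is sound: N=100 fits PGIC alone at two-sided .05.

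The exposure, if success could be claimed on any of the three, runs from about 5% to between 12.5% and 14.3%, depending on the undefined scope of the correction and on assumed correlations of 0.5 to 0. The 37% count lacks both a power statement and a clearly assigned analysis; its detectable difference of about 25 to 29 points rests on assumed control rates of 10% to 40%. This should be settled before enrolment.

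**What to change.** Name one primary outcome, population and time point, and test it at two-sided .05. Bring Study Objectives, Validation Methodology, Enrollment Procedures and Statistical Methods into line with it. That includes the 3-month versus 6-month time point, and whether PGIC and the BPI apply to everyone randomized or to the diabetes-with-pain subset.

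**If PGIC at 3 months in all randomized participants is chosen**, N=100 stands, and the text should:
- reword the primary-endpoint, primary-objective and efficacy sentences in Validation Methodology and Enrollment Procedures so that the 37% count, at a stated time, is the key secondary outcome;
- test that count at .05 only after PGIC is significant, using the existing logistic regression with responder defined as reaching the 37% goal;
- relabel the BPI as secondary and its power statement as supportive;
- limit Benjamini-Hochberg to the remaining secondary measures and delete the sentence that leaves the significance threshold to a later calculation;
- state that any health-risk claim rests on the 37% outcome.

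**If the 37% count is chosen**, replace the power statement with its detectable difference at 50 per arm and 85% power: about 25 points at an assumed 10% control rate, 28 at 20%, and 29 at 30% to 40%.

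The cost is wording before first enrolment, with no added participants or visits. Under the second option, the stated power becomes less favourable.
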